***Sample Size***

The aim is to enroll a total of 200 subjects with randomization to either the intervention arm or the control arm of the study (100 controls and 100 interventions). The study is powered to account for 10% loss to follow-up, with a target sample size of 180 patients. We calculated the sample size for the RCT by treating the Decision Process score of the DQI as continuous. We aimed to detect a treatment effect size (i.e., Cohen’s D) as small as 0.5 (consistent with preliminary data from the first 26 subjects we have studied) with a type I error rate of 0.05 and power of 0.90, assuming equal sample size in intervention and control groups. Given our 8 randomization strata, we estimate a needed sample size of 180 participants, or 90 for each group. With an estimated loss-to-follow-up rate of 10%. Our target enrollment for the RCT is 200 participants, or 100 for each arm.

***Timeline***

Recruitment Start: February 2021

Projected Recruitment End: August 2022

Projected Follow-Up End: November 2022 (follow-up at 3- and 6-9 month time points)

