**Administrative Information**

***Trial Information***

Trial Number: NCT04805554

Trial Registry: ClinicalTrials.gov

Date of Registration: March 18, 2021

Contact: [name] [contact]

Funding: AHRQ Grant R21HS027037

Coordinating Center: Dell Medical School at the University of Texas Austin

Ethics Review: Initial approval by UT IRB on February 21, 2020 (#2018110042, modifications approved later)

Study Type: Interventional

Study Design: Randomized parallel assignment open label (unblinded) study

Sample Size: 200

Date of First Enrollment: February 22, 2021

Recruitment Status: Enrolling

Expected Completion: June 2022

Sponsor: The funder (AHRQ) has no role in study design, collection, management, analysis, or data interpretation. The funder has no role in the writing of the report or the decision to submit the report for publication.

Principal Investigators: [name]; [name]; [name]

Grant Holders: [name] and [name]

Protocol: Dell Medical School: [name] (KJB), [name] (LU), [name] (PJ), [name] (EL), [name] (ZT), [name] (KMK) [name] (PR). UT Health Science Center San Antonio: [name] (JT)

Roles: Clinical trial design / conception: PJ, JT, KJB, PR, KMK; Study initiation: PJ, JT, KJB, LU; Study implementation / operations: EL, ZT, KMK, KJB; Statistical analysis: PR; Study protocol and refinement: All authors; Synthesis of data analysis: All authors; Approval of final manuscript: All authors.

Data Management: PJ, [name]

Recruitment: EL, ZT

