***Outcomes***

This study will assess the impact of a technology-enabled decision aid on:

| **Outcome** | **Measure** |
| --- | --- |
| Decision quality | Knee Decision Quality Index Q3.1-3.5 |
| Concordance | Knee DQI Q1.6 & whether patient had TKA within 9 months (Athena) |
| Shared decision making | CollaboRATE survey |
| Patient/provider satisfaction with discussion | Satisfaction question |
| Consultation time | Duration of surgeon/patient consultation in minutes as measured by research assistant |
| Overall health | PROMIS Global 10 |
| Change in limitations | KOOS JR |
| Treatment selected | Treatment choice/arthroplasty rate |
| Decisional conflict | Decisional Conflict Scale 10 (low literacy) |
| Decision regret | Decision Regret Scale |

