***Study Methods: Follow-Up***

Emails from REDCap will be sent automatically at 3 and 6 months after the baseline visit. We will send up to 3 emails (approximately 7 days apart) with a link to complete follow-up PROMs. If there is not response by approximately 3 days after the third email, a researcher will call the patient up to 3 times to complete the follow-up surveys via telephone.

- Follow-Up Surveys to complete at 3 and 6 months
  - KOOS JR
  - PROMIS Global 10
  - DRS
- Time Windows
  - 3 month follow-up window: 2.75 to 4 months after baseline visit.
  - 6-9 month follow-up window: 5.75 to 10 months after baseline visit.
- For patients for whom Spanish is indicated as the preferred language, the research assistant will call using the interpreter service.
  - To call the interpreter service:
    - Dial [name]
    - Enter 1755794
    - Enter MSKI PIN: 1115
    - Select Language: Spanish
    - Connect & conduct follow-up questionnaires using interpreting service

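### Follow-up is projected to end about three months after recruitment ends, too soon for the late enrollees' 6-9-month surveys and 9-month TKA status

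*Protocol*

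**What the plan says.** The Timeline section of the protocol gives "Projected Recruitment End: August 2022", followed by "Projected Follow-Up End: November 2022 (follow-up at 3- and 6-9 month time points". The second line therefore presents November 2022 as covering both follow-up points.

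Four other sections bear on these dates:

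- Study Methods: Follow-Up sets the windows relative to each patient's own visit: "3 month follow-up window: 2.75 to 4 months after baseline visit" and "6-9 month follow-up window: 5.75 to 10 months after baseline visit".
- Outcomes defines concordance from a DQI item together with "whether patient had TKA within 9 months (Athena".
- Data Management & Analysis plans longitudinal models that yield a treatment effect at 3 months and another at 6-9 months.
- Trial Information gives "Date of First Enrollment: February 22, 2021" and "Expected Completion: June 2022".

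The Interventions section schedules both follow-up points in both arms. No section says that late enrollees are followed only to 3 months or are cut off administratively.

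**The concern.** A patient enrolled in August 2022 cannot reach a window that opens at 5.75 months, still less a 9-month horizon, by November 2022. The completion date under Trial Information falls before recruitment is due to end.

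The outcomes at stake are KOOS JR, PROMIS Global 10 and decision regret at 6-9 months, and concordance, which depends on 9-month TKA status. If data collection or chart review stopped at the stated date, these would be incomplete for a block of patients defined by when they enrolled. Concordance carries a further risk. A patient who wanted surgery but has been observed for less than 9 months may have no TKA on record yet, and would look discordant if the gap were read as no surgery.

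**Working it through.** **Inputs**

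- First enrolment 22 February 2021; completion June 2022 (Trial Information).
- Recruitment end August 2022; follow-up end November 2022 (Timeline).
- 3-month window 2.75 to 4 months; 6-9-month window 5.75 to 10 months (Study Methods: Follow-Up).
- TKA horizon 9 months (Outcomes).
- Enrolment 200 (Sample Size).
- Assumptions: 1 month = 30.4375 days; uniform accrual. The Timeline gives months only, so the first and last day of each month are both tried.

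**Step 1: reproduce November 2022.** Last enrolment + 3 months gives 31 October 2022 (from 1 August) to 30 November 2022 (from 31 August). The stated end therefore matches the 3-month visit of the last enrollee and no later one.

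**Step 2: time available.** The longest possible interval, 1 August to 30 November 2022, is 121 days, and 121 / 30.4375 = 3.98 months. The later window opens at 5.75 × 30.4375 = 175 days. No choice of days within the stated months closes this gap.

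**Step 3: dates the last enrollee needs**

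| Milestone | Enrolled 1 Aug 2022 | Enrolled 31 Aug 2022 |
|---|---|---|
| 6-9-month window opens (5.75 months) | 23 Jan 2023 | 22 Feb 2023 |
| TKA horizon (9 months) | 2 May 2023 | 1 Jun 2023 |
| 6-9-month window closes (10 months) | 1 Jun 2023 | 1 Jul 2023 |

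**Step 4: patients affected if the stated dates were kept.** The latest usable enrolment date is the follow-up end minus the horizon. The share affected is the number of days from that date to the recruitment end, divided by the length of accrual. Accrual is 525 days to 1 August 2022 or 555 days to 31 August 2022.

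| Horizon | Follow-up end | Recruitment end | Latest usable enrolment | Share | Of 200 |
|---|---|---|---|---|---|
| 5.75 months | 30 Nov | 1 Aug | 8 Jun 2022 | 54/525 = 10.3% | 21 |
| 5.75 months | 30 Nov | 31 Aug | 8 Jun 2022 | 84/555 = 15.1% | 30 |
| 5.75 months | 1 Nov | 31 Aug | 10 May 2022 | 113/555 = 20.4% | 41 |
| 9 months | 30 Nov | 1 Aug | 1 Mar 2022 | 153/525 = 29.1% | 58 |
| 9 months | 30 Nov | 31 Aug | 1 Mar 2022 | 183/555 = 33.0% | 66 |
| 9 months | 1 Nov | 31 Aug | 31 Jan 2022 | 212/555 = 38.2% | 76 |

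**Step 5: the reverse check.** To keep November 2022, enrolment would have to close by about 10 May to 8 June 2022 for the last window merely to open, and by about 31 January to 1 March 2022 for 9-month TKA status. November 2022 is exactly 9 months after February 2022, so a wrong recruitment end would explain the mismatch as well as a wrong follow-up end.

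**The case against.** The strongest reply is that both Timeline dates are labelled as projections and neither is a stopping rule. The survey windows run from each patient's own visit, and staff schedule both follow-up emails at baseline for patients who prefer email. Staff who follow those instructions would survey an August 2022 enrollee in 2023. TKA status comes from the medical record, which can be read later. All of this stands, so it would be too strong to say that the data cannot be collected. What remains is that they cannot be collected within the stated timeline.

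A second reply is that any loss would be by calendar date. Blocks within strata keep the arms balanced through time, so survey losses should be similar in the two arms and would mainly cost precision on secondary outcomes. That also stands.

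A reader might go further in four ways that the document does not support:

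- **That truncation uses up the 10% loss allowance and weakens the trial's power.** The allowance belongs to a calculation on the DQI Decision Process score. The DQI is completed straight after the consultation, so a calendar cut-off does not remove it. No power is claimed for any 6-9-month outcome.
- **That unobserved patients will be coded as having no TKA.** No section says so, and a coding rule may sit in an analysis plan that is not shown. Any figure for the share of TKAs missed would need an assumed distribution of surgery times, which the protocol does not give.
- **That everyone short of 10 months is lost.** A survey answered at any time in the 5.75-10-month window counts, so only patients whose window never opens are certain losses.
- **That the follow-up end is the wrong date.** The document does not show which date is wrong.

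**Conclusion.** The point holds as a contradiction among the protocol's own dates. November 2022 accommodates the last enrollee's 3-month visit but not the 6-9-month window, the 9-month TKA horizon or the planned 6-9-month treatment effects. June 2022 as a completion date fits none of them, although the protocol does not say what is completed then.

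The contradiction itself needs no assumption, because it is true for every day within the stated months. The patient counts in Step 4 do need two: uniform accrual, and operations that actually stop at the stated end. A different accrual pattern would change them.

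The harm is confined to the secondary 6-9-month KOOS JR, PROMIS Global 10 and decision regret outcomes and to concordance. It is more than clerical, because a team that locked data on the stated date would lose a material share of those outcomes. The primary comparison is untouched.

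**What to change.** Reconcile the Timeline and Trial Information dates with the Outcomes and Study Methods: Follow-Up sections, in one of two ways:

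- Keep recruitment to August 2022 and set the end of follow-up at 9 months after the last enrolment for TKA status and up to 10 months for surveys, which is about May to July 2023.
- If August 2022 is the wrong date, correct the recruitment end so that November 2022 leaves the follow-up needed (Step 5 gives the latest enrolment dates).

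In either case, bring the June 2022 completion date into line. State that TKA status is abstracted from the chart only after a patient has reached 9 months, so that incomplete chart follow-up is not counted as no TKA.

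The cost is a few date edits, one sentence on abstraction and, under the first option, a later data lock. No additional patients are needed.

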***Recruitment & Follow-Up Flowsheet***
[figure not shown]

***Recruitment methods: Eligibility Screening***

Patients will be identified as suitable candidates for the study by members of the research team during the pre-clinic meeting (huddle). Initial decisions will be made based on appointment type, chief complaint, age, availability of radiographs, and availability of a recent BMI.

Once the patient has completed any required imaging, entered the clinic room or private consultation space, and been checked in by the Medical Assistant (including measurement of height and weight), the researcher will confirm that the patient meets all inclusion criteria and none of the exclusion criteria. At this time, the researcher should record the patient’s height and weight to facilitate enrollment in the OM1 tool. Additionally, the researcher should prepare translation services if necessary. The researcher will then approach the patient and invite him or her to participate in the study.

- Eligibility Screening Documentation
  - All new patients with a presumptive diagnosis of knee OA aged 45-89 will be entered into the Excel worksheet **“Joint Insights Eligibility Screen”** (in Box)
  - Documentation will include:
    - Enrollment Status:
      - Consented (Y/N)
      - Screen Fail (Y/N)
      - Reason for screening failure:
        - Not OA
        - Prior TKA
        - Prior discussion with an orthopaedic surgeon about TKA
        - Previously seen/used Joint Insights
        - Considering revision joint replacement
        - Seeking care for trauma condition
        - Non-English or Non-Spanish speakers
        - K-L Joint space narrowing grade 1 or 2
        - KOOS JR score >85
        - BMI below 20 or above 46
        - Age under 45 or over 89
        - Unable to give informed consent
        - Other
      - Declined (Y/N)
      - Reason for declining:
        - Not enough time
        - Privacy concerns
        - Not interested
        - No reason given
        - Other (record reason)

***Recruitment methods: Informed Consent***

If the patient qualifies for the study, the researcher will obtain informed consent by adhering to the following script as much as possible:

***Recruitment methods: Randomization***

The researcher will then enroll the patient and perform randomization using the REDCap online platform. Patients will be informed if they are in the intervention group (“Full Tool”) or control group (“Edu Only”). Researchers will do their best to follow standard scripts for each step of the recruitment as below.

- Prior to entering the room, the researcher should:
  - Open and log into REDCap
  - Open and log into OM1
- REDCap randomization procedure on clinic iPads, in room with patient:
  - From the REDCap homepage, enter the “Joint Insights” project
  - Go to Add/Edit Records on the left hand side of REDCap, then “Add new record”
  - Complete the “Informed Consent and HIPAA” record, including a signature
  - Complete the **first three items** on the “Enroller: Initial Visit Details” record
    - Site & clinic-associated surgeon ([name] vs [name])
    - Is the patient Hispanic? (Y vs N)
    - What kind of insurance? (MAP/Medicaid vs Other)
  - Click the “Randomization” button, which will show either:
    - “Group A – Full tool”
    - “Group B – Educational materials only”

[figure not shown]

- - Inform the patient as to the group into which they have been randomized
    - *FULL TOOL: “You have been selected to receive the educational materials and the software. Let me briefly talk you through the process. Please kindly read the education material on this iPad at your own pace, answer the questions at the end, and use the sliders to tell us about your preferences and experiences. You will then receive a report customized to you which can guide discussion with your provider. Please feel free to ask any questions during this consultation. Thanks in advance for completing some survey questions on how it all went at the end of the visit, please be sure to wait for me to return before leaving.”*
    - *EDUCATION ONLY: “You have been selected to receive the educational materials. Let me briefly talk you through the process. Please kindly read the education material on this iPad at your own pace. You will then have a chance to discuss your problem and treatment options with your provider. Please feel free to ask any questions during this consultation. Thanks in advance for completing some survey questions on how it all went at the end of the visit, please be sure to wait for me to return before leaving.”*

***Recruitment Methods: OM1 Enrollment & Delivery***

After Randomization, leave REDCap and open instead the online OM1 platform in a new browser tab. Follow the procedure below to enroll the patient and open the education:

- Click “Add Patient” in the top menu bar
- Complete only the fields in the REGISTRATION and CONTACT PREFERNCES sections marked with an Asterix *
  - First name
  - Last name
  - Date of birth
  - Sex at birth
  - Language Preference
- Click “Continue”
- Complete all fields in the CARE TEAM section
  - Organization (UT Health Austin)
  - Physicians ([name] vs [name])
  - Musculoskeletal (L vs R knee)
- Click “Save”
- Complete all fields with an Asterix * in the [RIGHT/LEFT] KNEE section
  - Type
    - “TKA Consultation” if patient is in Group A / Full tool
    - “TKA Education” if patient is in Group B / Educational materials only
  - Event date (today)
  - Facility (UT Health Austin)
  - Physician ([name] vs [name])
  - *If patient is randomized to the Full Tool, the below fields will also appear, which the researcher will then complete using the medial chart or by speaking directly with the patient:*
    - Height (manually enter from chart)
    - Weight (manually enter from chart)
    - Tobacco use (select one)
    - Comorbidities (select all that apply)
    - #ED visits in the last year
    - #Hospitalizations in the last year
- Click “Save”
- The following screen will automatically appear after a few moments:

[figure not shown]

- - Click the dropdown menu “Send PRO to” and select “transfer to paper”

[figure not shown]

- - Enter the patient’s birth date and today’s date to open the module
  - The educational module will automatically appear, and the researcher will then hand the iPad to the patient for them to navigate through at their own speed. Researchers will use the following script:
    - *FULL TOOL:* “*This educational module should take about 5-10 minutes to read through, depending on your pace. When you are ready to move on to the next section, simply press “next” in the lower right-hand corner. When you reach the end of the education there will be a short quiz but do not worry, it is not graded. It is simply to help you test your own knowledge of what you learned. There will also be a few questions about your treatment preferences. Again, those are only for your benefit to help you think about the treatment options. There is no “right” answer. Finally, you will reach a set of survey questions identical to the ones you already answered in the lobby where you checked in. You may stop there, and I will fill out the survey using the information you have already given us. I will be back in 5-10 minutes and would be happy to answer any questions you have at that time.”*
    - *EDUCATION ONLY:* “*This educational module should take about 5-10 minutes to read through, depending on your pace. When you are ready to move on to the next section, simply press “next” in the lower right-hand corner. When you reach the end of the education there will be a short quiz but do not worry, it is not graded. It is simply to help you test your own knowledge of what you learned. I will be back in 5-10 minutes and would be happy to answer any questions you have at that time.”*
- Leave the room for 5-10 minutes
  - *Optional:* while patient is reading over the iPad materials, the RA completes the patient’s OM1 profile utilizing individual patient-reported outcome measure question responses to the KOOS, JR and PROMIS-10 Global as viewable in AthenaHealth.
  - The RA may also create a second module for patients reporting bilateral knee pain who are randomized to the full tool, so that the patient can get individualized scores for each side
- Return when time is up, and check if the patient has completed the educational module
  - If the patient is not done, politely offer more time
  - If the patient is done:
    - Close the tab with the educational module
    - *For education + preferences only patients:*
      - Thank them and leave the room
      - Inform the provider the patient is ready to be seen
    - *For full tool patients:*
      - Return to the OM1 enrollment tab and click “View Surgery Benefit & Risk Report”

[figure not shown]

- - - - This will open a new tab with the Joint Insights report
      - Click on the “Select OA severity” dropdown menu to select the radiographic severity (KL 3 or 4)
      - Show the results with the patient and explain that they will receive a printed-out version for discussion with their provider
      - Leave the room
      - Print out the score report(s) and hand to the provider or hang in the basket on the exam room door
      - Inform the provider the patient is ready to be seen
      - Write the patient’s “Benefit” percentage under “notes” on the clinic whiteboard
- During the provider consultation
  - Research assistant must record for REDCap:
    - The number of minutes the counseling provider was in the room
      - This includes [name], [name], the Arthroplasty Fellow, Advanced Practice Providers (APPs).
      - As much as possible, the amount of time should only reflect time spent on the shared decision making conversation; this means that time spent on injections does not count, and time spent collecting medical history should not contribute either
      - However, we recognize there is variation in which provider or learner contributes to each part of the visit – for instance a learner (medical student or resident) might collect history for some patients which will *not* be included in the final time calculation, while the APPs might collect history for others and this *will* be included
      - Ultimately, we just record the exact number of minutes any of the above providers who are listed specifically by name spend in the room *except* after they come out to grab an injection and go back in to perform the injection
    - Enter the total consultation minutes into the appropriate field in REDCap
  - If the exact timing is missed, RA will confirm an estimate with the provider

***Recruitment Methods: Baseline Visit Questionnaires***

Patients from both randomization arms will be asked to complete the baseline surveys in REDCap at the end of their visit as soon as the consultation with their provider is complete:

- Patient Questions: Demographics
- Patient Questions: DQI
- Patient Questions: CollaboRATE
- Patient Questions: DCS10
- Patient Question: Satisfaction
- Patient-Facing Done Page (ask for patient preference of phone vs email for follow-up)

Researchers will then ask the relevant provider for the visit to complete the baseline survey in REDCap:

- Provider Question: Satisfaction

***Study Methods: Baseline Documentation***

The following steps must be completed by the researcher at the baseline visit to ensure proper documentation:

- On Box
  - Completion of the “Joint Insights Eligibility Tracker” as above
  - Completion of the “Joint Insights Follow-Up Tracker” for all enrolled patients
  - Completion of the “Joint Insights Dashboard” with total number of patients enrolled
- On REDCap
  - Completion of all baseline surveys (in “Event 1” column)
    - Complete “KOOS, JR” using Athena
    - Complete “PROMIS-10” using Athena
  - Mark which knee is primary in the 3-month “Follow-Up KOOS, JR” field
  - Mark which knee is primary in the 6-9 month “Follow-Up KOOS, JR” field
  - Schedule emails for the 3- and 6-9 month follow-up visits for patients preferring emails rather than phone calls
    - Schedule for a date 7 days before the 3-month follow-up date
    - Set up to 2 recurring reminders, each 7 days apart
    - Use the [[contact]](mailto:[contact]) email as the sender
    - Use the “Email Template” found on Box for the body of the email
      - Change [NAME] to the patient’s last name
      - Change [DATE] to the patient’s 3-month follow-up date

